#### Subgroup analysis

Two explorative, pre-defined, subgroup analyses will be performed assessing the interaction effects between treatment and the severity of baseline pain (SPADI pain subscale) and between treatment and baseline function (SPADI function subscale) on the primary and secondary outcomes.

#### Sensitivity analysis

To test the robustness of the results sensitivity analysis will be performed using per-protocol principles (excluding participants with cross-over during the study period) and using complete cases only.

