#### Co-interventions

This is a pragmatic clinical trial designed to evaluate the effectiveness of corticosteroid injections compared with physiotherapist-led exercise therapy for shoulder pain in real-life routine practice conditions. Therefore, participants will be instructed to continue their usual medication as discussed with their GP. Co-interventions after randomisation will be allowed and will be monitored through medical record review and questionnaires. This includes cross-over between interventions, which is estimated to occur in 20% of participants based on the number of patients receiving an injection and referral for exercise therapy in the ‘usual care’ treatment arm of a recent RCT.^15^

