### Sample size

The target sample size is 85 participants in each trial group. This is based on 90% power and a 0.05 two-sided statistical significance to detect a minimally clinically important difference of ten points on the SPADI total scale,^24^ using a conservative estimation of a baseline SD of 20.^25^ Accounting for a potential loss to follow-up at 12 months of 20%, this will require a total of 213 patients to be randomised to the intervention groups.

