### Blinding

The researcher who will carry out the primary analysis will be blinded for treatment allocation. The participant and the GP will not be blinded for treatment allocation. This is not feasible in this pragmatic trial.

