### Statistical methods

Baseline characteristics will be summarised using descriptive statistics. All analyses will be performed under intention-to-treat.

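### Excluding everyone who crosses over makes the per-protocol sensitivity analysis hard to read as a robustness check if cross-over is related to SPADI and differs by arm

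*Protocol article*

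**What the plan says.** Under Statistical methods the article states: "All analyses will be performed under intention-to-treat". Under Sensitivity analysis it adds two further analyses. Their purpose is given as "To test the robustness of the results sensitivity analysis will be performed". One uses complete cases; the other uses "per-protocol principles (excluding participants with cross-over during the study period".

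Under Co-interventions the article treats switching as part of the pragmatic design: "Co-interventions after randomisation will be allowed and will be monitored through medical record review and questionnaires". It continues: "This includes cross-over between interventions, which is estimated to occur in 20% of participants". That figure is taken from the usual-care arm of another trial. No reasons, timing or split by arm are given. Under Blinding: "The participant and the GP will not be blinded for treatment allocation".

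**The concern.** Cross-over happens after randomisation and is allowed, so a participant who crosses over has not departed from the protocol. Removing all of them takes out about one participant in five, chosen by something that may depend on how they were doing. It also removes their valid SPADI values from before the switch. Someone who switches in month 8 loses the 6-week, 3-month and 6-month scores as well.

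There are grounds to expect a link with outcome. The Introduction describes a stepped-care guideline in which injection or exercise referral follows persisting pain, and participants and GPs know the allocation. There are also grounds to expect different switching by arm. The injection is typically given within a week, with a possible second one 2 to 4 weeks later, while exercise runs over 12 to 14 weeks. The occasion and timing for switching therefore differ.

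If both conditions hold, the retained arms differ for reasons other than treatment. A real difference could be diluted, or a difference could appear where there is none, and the result would then be reported as a check on the primary finding. The Discussion expects the trial to inform guidelines and possibly reimbursement, so readers may take a per-protocol figure as the effect of the treatment actually received.

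**Working it through.** **1. The plan's own figure.** Inputs from Sample size: difference 10, SD 20, "90% power and a 0.05 two-sided statistical significance", loss 20%. By the normal formula, n = 2 × (1.960 + 1.282)² × 20² / 10² = 84.1, rounded up to 85 per arm (t-based: 85.03). Then 170 / 0.8 = 212.5, rounded up to 213. Both stated figures reproduce.

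**2. What the exclusion leaves.** With 20% removed, 85 × 0.8 = 68 per arm. The standard error rises from 20 × √(2/85) = 3.07 to 20 × √(2/68) = 3.43. Nominal power for 10 points falls from 90.3% to Φ(10/3.43 − 1.96) = 83.0%.

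**3. Direction and rough size with no true effect.** Suppose a normal cross-over propensity has correlation ρ with the outcome (higher is worse), and the top fraction p of an arm is removed. The retained mean shifts by −ρ × 20 × φ(z) / (1 − p), where z is the (1 − p) normal quantile.
- p = 0.30: 20 × 0.348 / 0.70 = 9.93, so the shift is −3.0 (ρ = 0.3) to −7.0 (ρ = 0.7).
- p = 0.10: 20 × 0.1755 / 0.90 = 3.90, so the shift is −1.2 to −2.7.
- Spurious difference at 30% v 10%: 1.8 to 4.2 points, in favour of the arm with more cross-over. Simulation gives the same, with a false-positive rate of 8% to 27%.
- 20% v 20%: each arm improves by 2.1 to 4.9 points, and the difference between arms is 0.
- ρ = 0: no bias for any split.

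The arm split and ρ are assumptions.

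**4. Simulation with repeated visits.** Assumed: SD 20; correlation 0.6 between follow-up visits and 0.4 with baseline; overall cross-over 20% after 3 months; log-odds of cross-over linear in 3-month SPADI; cross-over itself without effect. The slope is unknown, so three values are shown. They correspond to odds ratios per 10 points of e^0.3 = 1.35, e^0.5 = 1.65 and e^1.0 = 2.72. Each cell gives the range over three summaries: 12 months unadjusted, 12 months adjusted for baseline, and the mean of five follow-up visits.

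| Slope per point | True 10, one common rule | True 10, 30% v 10% | True 0, 30% v 10% (size of spurious difference) |
|---|---|---|---|
| 0.03 | 9.5–9.7 | 8.5–9.0 | 0.9–1.4 |
| 0.05 | 9.2–9.6 | 7.9–8.6 | 1.5–2.1 |
| 0.10 | 8.4–8.9 | 6.8–7.9 | 2.1–3.1 |

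With a true difference of 10 and exactly 20% cross-over in each arm, the exclusion returned 9.97 to 10.02 at 12 months. Under a common rule the worse arm switches more (about 25% v 15% at slope 0.10), which is why the difference shrinks.

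Subtracting from 10, and allowing 0.1 to 0.2 for variation between repeat runs, the bias is 0.2 to 1.6 points under a common rule. At 30% v 10% it is about 1.4 to 3.2 on the five-visit mean. It is smallest for the baseline-adjusted 12-month value, about 1 point at the shallowest slope.

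**5. The alternative.** Keeping everyone, using SPADI up to cross-over and treating later values as missing returned 9.9 to 10.1 for a true 10, and within 0.2 of zero for a true 0. When cross-over was made to depend on a 6-month score that the censoring hides, this estimate was off by up to 0.6, still less than the exclusion.

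**The case against.** A reader might infer that cross-over is driven by poor response, that the analysis is therefore biased, and that it cannot test robustness. The documents do not support any of the three in that form.

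- **Cause.** The article gives no reasons for cross-over. Preference could also play a part: the Parallel cohort study section mentions strong treatment preferences, though as a reason to decline randomisation. A link with response is an inference.
- **Certainty.** The bias is conditional. It is zero when cross-over is unrelated to outcome, and about zero when both arms cross over equally by the same mechanism. The 30% v 10% split is assumed.
- **Size.** The largest figures need a steep slope. Under a common rule the bias (0.2 to 1.6) is less than half of the 3.43-point standard error with 68 per arm.
- **Consequence.** Primary inference is by intention to treat. This is one of two supplementary analyses, its exclusion is openly stated, and no conclusion is tied to it.
- **The alternative.** Its near-exact recovery follows from generating cross-over from a score that the model conditions on. Because cross-over had no effect in the simulation, intention to treat recovers the same truth, so the example shows the fault of the exclusion and no gain over the primary analysis.

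All of this stands and limits the point. A further argument is that such detail belongs in an SAP that is not shown. That covers details of weighting and labelling, but the exclusion rule itself is fixed in the article. Nor does equal cross-over rescue the rule in general: if a treatment effect exists and one rule links switching to pain, the arms will not switch equally.

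**Conclusion.** The point holds in conditional form. The article fixes a rule that excludes participants for an event it permits and expects in 20%, with no adjustment for the resulting selection. The exclusion answers a different question from intention to treat, and does so under a strong, unstated assumption about switching. Agreement with the primary result would not show robustness, and disagreement would not show fragility.

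Against the 10-point target, the plausible distortion runs from nothing to about 3 points in the visit-based simulation, depending on an arm split and a strength of association that the article does not give. The primary estimate, its power and its error rate are untouched, so this is an improvement to a supplementary analysis and not a threat to the trial's main conclusion.

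**What to change.** Replace the exclusion, or at minimum accompany it, with an analysis that keeps all randomised participants in the mixed model described under Primary analyses, uses SPADI up to cross-over and treats later values as missing. Inverse-probability weighting on time-varying SPADI may support it. Label the result as a supplementary estimate of the difference had no cross-over occurred, and state its assumption. Report the number and timing of cross-overs by arm beside it, so that readers can judge how much selection is possible. If the exclusion is kept, label it exploratory.

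The cost is a change of wording and modest analysis work. The cross-over date must be extracted from the medical records and questionnaires already used for monitoring; the article promises a recorded date only for a second injection. The new estimate is unbiased only if cross-over is explained by recorded SPADI and covariates, which is still a weaker assumption than the exclusion needs.

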### Data monitoring

This study has negligible risk according to the risk classification published in the guidelines of the Dutch Federation of University Medical Centres.^31^ Therefore, monitoring will take place once a year by independent monitors and no Data Monitoring Committee will be assigned to this study. Trial conduct and data integrity will be audited once per year by independent auditors.

### Harms

Potential adverse events will be monitored using patient self-report questionnaires, contact with the SIX research team and GP reports. GPs and physiotherapists will be asked to report any SAE and suspected unexpected serious adverse reaction (SUSAR) directly to the SIX research team. The SIX research team will report the SAE or SUSAR to the the Medical Research and Ethics Committee (METC).

### Patient and public involvement

Prior to the design of this trial, patients who recently consulted their GP for shoulder pain were contacted to participate in our patient panel. These patients could comment on the design and confirmed this study as relevant and feasible. The patient panel will also be used to help facilitate dissemination of the final results to trial participants and in the design of implementation strategies towards patients.

## Ethics and dissemination

### Ethics approval and informed consent

Ethical approval on this protocol (V.3.0) was obtained on 18 September 2020 by the METC of Erasmus MC University Medical Center Rotterdam (MEC 2020-0300). Any substantial amendment made to the protocol by the coordinating investigator is sent to the METC for approval, prior to implementation. All participants will give written informed consent prior to data collection (online supplemental file).

10.1136/bmjopen-2021-050101.supp1Supplementary data

### Dissemination

Results of this trial will be published in peer-reviewed journals, as a double publication in a national GPs journal, to the Royal Dutch Society for Physiotherapy (KNGF), and through social media. A patient panel composed by the research team consisting of patients with shoulder pain will help facilitate the optimisation of the method of dissemination of the results to participating patients. Furthermore, participating GPs and physiotherapist will be informed about trial results (expected in 2023).

## Discussion

This paper presents the design of a pragmatic, RCT that will assess the effectiveness of corticosteroid injection versus physiotherapist-led exercise therapy for shoulder pain in primary care. Furthermore, this trial will assess the cost effectiveness of both interventions from a societal and healthcare perspective. The primary outcome is shoulder pain-intensity and function measured with the SPADI over a 12-month period. Secondary outcomes are measured at 6 weeks, 3, 6, 9 and 12 months follow-up and include shoulder pain-intensity, shoulder function, global perceived effect, quality of life, sleep quality, work absence, healthcare utilisation and adverse reactions. Between group differences for the primary outcome will be evaluated using a repeated measurements analysis with linear mixed models. An economic evaluation will be performed using a cost-utility analysis with quality of life. The outcomes of this trial may impact the clinical guideline recommendations for the management of shoulder pain in primary care and possibly the reimbursement of physiotherapy for patients with shoulder pain. Recruitment of eligible patients is currently ongoing (November 2020). Substantial protocol amendments will be communicated to participants, cooperating GPs and physiotherapist, the METC, the Dutch Trial Registry, ZonMw and the journal publishing this protocol.
